## Methods

### Aims

This randomised controlled trial protocol investigates the cost-effectiveness of an integrated care pathway between hospital and primary care partnerships in improving health and social outcomes in children with chronic health conditions. More specifically, our objectives are to: (1) determine if the ICCC results in better health outcomes for children with chronic health conditions, compared to a self-directed care pathway; and (2) determine the cost-effectiveness of the ICCC using health economics data. We hypothesize that: (a) Children who access the ICCC will have improved quality of life and behavioural scores than children who access the self-directed care pathway; and (b) the ICCC pathway is more cost-effective than the self-directed care pathway.

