#### Self-directed care pathway

The procedure for self-directed care pathway is similar to ICCC, except the participants will not have access to an AHLO to: (a) coordinate GP appointments at 1 week, 3 and 6 months post Paediatrician appointment, and (b) assist with any communication and access issues that arise during the duration of the study.

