### Statistical analyses

All analyses will be conducted using an “intention to treat” (ITT) analysis where all subjects will be compared in the groups which they were originally assigned (regardless of withdrawal or lost to follow-up). For our primary objective, Mann Whitney U test will be used to determine if differences in quality of life measures exist between the ICCC versus self-directed care groups.

For our secondary objective, we will perform univariable analysis to determine which health economic parameters (e.g. missed school days, number of hospital admissions) are related to higher quality of life scores. Stepwise regression will then examine the various combinations via of health economic parameters to generate area under receiver operating curves (aROC) to determine a clinical prediction index for higher quality of life scores. Parameters chosen will be based on using factors that were significant plus those with *P* < .25 level in the univariable analysis and other variables known to have a strong association with poorer health outcomes (e.g. multiple co-morbidities) within the literature. An aROC of ≥0.75 will be considered a clinically relevant cut-off score [23].

As this study is registered on the ANZCTR and occurring within Metro North Hospital and Health Service, the trial may be randomly audited by an independent study monitor at any timepoint in the study. A data monitoring committee will not be set up for the purposes of this study, as it is unblinded and not comparing rates of mortality or major morbidity.

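### The secondary-objective screen and stepwise index relate post-randomisation resource counts to quality of life with no term for randomised arm, so a count that only marks the arm can pass too often and a real association can be diluted

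*Protocol article*

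**What the plan says.** All references are to the protocol article.

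- **Statistical analyses, screen.** The secondary objective is served by "univariable analysis to determine which health economic parameters (e.g. missed school days, number of hospital admissions) are related to higher quality of life scores".
- **Statistical analyses, model.** Stepwise regression over combinations of these parameters follows, "to determine a clinical prediction index for higher quality of life scores".
- **Statistical analyses, entry rule.** Three classes of candidate are named: significant factors, anything below .25 in the screen, and literature variables tied to worse outcomes. The rule opens with "Parameters chosen will be based on using factors that were significant plus those with". Randomised arm is not named as a candidate, adjustment, stratum or interaction, and no index per arm is described.
- **Statistical analyses, performance.** An aROC of at least 0.75 "will be considered a clinically relevant cut-off score".
- **Statistical analyses, general rule.** Under intention to treat, "all subjects will be compared in the groups which they were originally assigned".
- **Outcome measures.** GP visits, admissions, specialist appointments, absent school days and services accessed are the trial's own secondary outcomes, recorded from 1 week onwards.
- **Self-directed care pathway.** Control families have no liaison officer to "coordinate GP appointments at 1 week, 3 and 6 months post Paediatrician appointment".
- **Aims.** The hypothesis is that "Children who access the ICCC will have improved quality of life and behavioural scores than children who access the self-directed care pathway".

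**The concern.** On the trial's own hypotheses, arm acts on both sides of the regression. It moves at least one candidate predictor (GP visits, arranged in one arm only), and it is expected to move the outcome. If the arms are analysed together without an arm term, the association between count and quality of life mixes two things: the relation among children on the same pathway, and the difference between pathways.

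Two errors follow. A count with no relation to quality of life within either arm can look like a predictor because it marks who received ICCC. Conversely, if sicker children make more visits and have lower scores, the arm difference pulls the other way and weakens that real association.

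At stake is the interpretation of the index. The Discussion wants the study to show which families manage the system themselves and which need more support. A count that stands in for trial arm does not answer that, and its arm-driven part has no meaning where all or none of the children receive ICCC.

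**Working it through.** **1. Design size.** From Sample size and statistical power: difference 15, 80% power, alpha 0.05, 50% attrition, total 112. The SD is not given; two-sided testing and 1:1 allocation are assumed.

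n per arm = 2 × (1.960 + 0.842)² × (SD/15)². With SD = 20 this is 27.9, so 28 per arm, 56 completers, and 56/0.5 = 112. The stated total is reproduced with SD 20 (SD 19 gives 104, SD 21 gives 124). The standardised effect is then 15/20 = 0.75. The SD is an inference, not a figure in the protocol.

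**2. Correlation created by arm alone.** Let arm shift quality of life by d_q and the count by d_c (in within-arm SDs), with no within-arm relation and equal arms. The pooled correlation is

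r = (d_q·d_c/4) / √[(1 + d_q²/4)(1 + d_c²/4)].

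For d_q = 0.75 and d_c = 1: 0.1875/√(1.1406 × 1.25) = 0.157.

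Simulated pass rates, no arm term (20,000 runs each):

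| Arm shift in count (SD) | r | P < .25, 56 children | P < .05, 56 children | P < .25, 112 children |
|---|---|---|---|---|
| 0.25 | 0.04 | 27.5% | 6.5% | 29% |
| 0.5 | 0.09 | 33% | 10% | 42% |
| 0.75 | 0.12 | 43% | 15% | 58% |
| 1.0 | 0.16 | 53% | 22% | 71% |
| 1.5 | 0.21 | 69% | 36% | 88% |

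With an arm term, every row returns to about 25% and 5%.

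**3. GP visits.** Assumed background mean 3 or 5, Poisson or overdispersed (variance = mean + 0.5 × mean²), 28 per arm, d_q = 0.75, no within-arm link:

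| Extra visits under ICCC | P < .25, no arm term | P < .05, no arm term |
|---|---|---|
| 1 | 27–37% | 6–11% |
| 2 | 34–58% | 9–26% |
| 3 | 42–74% | 15–42% |

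With an arm term: 24–26% and about 5% throughout. The two tables agree. For mean 5 overdispersed, the SD is √(5 + 12.5) = 4.18, so 3 visits is 0.72 SD and the rate is near the 0.75 SD row.

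**4. Sensitivity to the ICCC effect.** At half the design effect (0.375 SD), P < .25 rates run from about 25–28% with one extra visit to at most about 43% with three. At 0.25 SD they are at most about 33%. At zero effect there is no excess.

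**5. Dilution.** Assume a within-arm correlation of −0.3, overdispersed counts with mean 5, and 3 extra visits. The between-arm part of the covariance is 0.75 × 0.717/4 = 0.134, so the pooled covariance is −0.3 + 0.134 = −0.166. The pooled correlation is −0.166/√(1.1406 × 1.1286) = −0.15. Simulated detection falls from 61% with an arm term to 18% without at P < .05, and from 86% to 47% at P < .25.

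**6. Effect on the aROC.** For 3 extra visits and Poisson background means of 1 to 5, arm marking alone gives a single-variable aROC of about 0.60 to 0.64 for quality of life above the median. That is below 0.75.

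The screen was simulated as a linear association, because the article does not state the model type.

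**The case against.** **The article never says the arms are pooled.** This is correct. Pooling is inferred from the single index and from an entry rule that omits arm, and a reader who takes it as an explicit exclusion of arm goes further than the text. Adjustment terms are often left to an analysis plan, and an entry rule for candidates does not forbid forcing a design variable in. But the article itself fixes the candidate classes, the P threshold, the selection method and the performance criterion. Followed as written, it produces models without arm. The intention-to-treat sentence does not help, because it governs comparisons between groups and this regression compares none.

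**A prediction index need not be causal.** Also correct. Yet if arm carries predictive information, it should be offered openly and not through a proxy. The part of an association that comes from the arm contrast disappears where everyone is on one pathway.

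**GP consultations may be how ICCC works, so adjusting for arm removes part of the path.** They may be mediators. A model without arm cannot separate mediation from arm marking, however, and a mediation question would itself need arm in the outcome model.

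**The size rests on assumptions.** This stands. The SD, the background visits, the extra visits and the absence of a within-arm link are not in the protocol. GP visits are the count most directly tied to the intervention. For the two examples the protocol names, missed school days and admissions, it gives no expected difference between arms.

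**An arm term does not supply the cost-effectiveness comparison** that the second aim calls for. This is true, and the fix below does not claim to.

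**Conclusion.** The concern holds in a limited form. As described, the screen and index leave out an arm term where arm is designed to affect at least GP visits and is hypothesised to affect quality of life. A count that only marks the arm can therefore pass more often than its nominal rate, and a real within-arm association can be diluted.

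Under the stated assumptions (28 completers per arm, 0.75 SD effect, background mean 3 to 5, 1 to 3 extra visits, no within-arm link), GP visits pass P < .25 in about 27% to 74% of runs, against 25% with arm included. The excess shrinks markedly at half that effect and vanishes if ICCC does not change quality of life.

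A reader might infer more than this:

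- **That such counts will enter the index.** They can enter. For a 0.25 SD shift the rate is 27.5%, barely above the 25% for any null variable.
- **That every resource count is affected.** The protocol documents a designed difference for GP visits, not for school days or admissions.
- **That arm marking would produce an index meeting the 0.75 criterion.** One marker alone gives about 0.60 to 0.64.
- **That counts and quality of life are taken from the wrong time windows.** The protocol does not say which visit or window is used, so there is nothing to correct.

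The primary Mann-Whitney comparison and the sample size are unaffected.

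**What to change.** In Statistical analyses, or in the analysis plan if one exists:

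1. Force randomised arm into every univariable, stepwise and final model, or estimate the associations within each arm and pool them.
2. Apply the significance and P < .25 entry rules to each parameter's arm-adjusted association.
3. Label the prediction index exploratory.

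The cost is a few sentences and one degree of freedom per model. No new data are needed, and neither the sample size nor the primary analysis changes.

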### Safety considerations/patient safety

The study will be conducted in full conformance with principles of the Declaration of Helsinki [24] and Good Clinical Practice (GCP) [24]. Children randomised to the self-directed pathway will be allowed to change to the ICCC pathway after 6 months, if they wish. However, their recorded data at 12 months will not be used in the final analyses. Identified information will only be shared and viewed by investigators involved in patient care or data collection. De-identified information will only be seen by investigators on the project. Data will be stored in locked cabinet at Caboolture Hospital for 5 years post study completion, as per National Health and Medical Research Council (NHMRC) guidelines.

For caregivers who identify with literacy issues, the AHLO will ensure extra time is used to explain the study and obtain informed consent [17]. Before finalising consent, the AHLO will be required use the “teach back” method and ask the caregiver to explain in their own words what the research study is asking them to do, including risks and processes involved [18]. For children age ≥ 12 years, assent will be obtained for participation in the study in conjunction with caregiver consent.

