At 12 months (+/− 14 days) post Paediatrician appointment, medical students from each hospital will call the primary caregiver to complete: Peds QOL Child and Family Impact Modules, [20] SUDS and Locus of Control Questionnaire.

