#### Outcome measures

Primary outcome measures taken at 1 week, 3, 6, 12 months include**:** PedQOL child module (Score 0 to 100; parent or child completed), [20] PedQOL family impact module (Score 0 to 100; parent completed), [20] SUDS (Score 0 to 100; parent completed), CBCL (Percentiles, parent completed) [21] and Rotter’s Locus of Control Scale (Score 0 to 23, parent completed) [22].

Secondary outcome measures taken at 1 week, 3, 6, 12 months include the number of**:** GP visits, hospital admissions**,** specialist appointments**,** absent school days, caregiver missed employment days, school suspensions including duration in days and services currently accessed at the time.

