### Sample size and statistical power

We plan for a total sample size of 112 children (80% power to detect a mean effect difference of 15 between groups on the quality of life scale) at 0.05 significance level. This sample size has been adjusted for an anticipated high attrition rate of 50%. A 2-sample test of proportions will be used to compare baseline characteristics of both groups.

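### Dropping the recorded 12-month data of control children who switch to ICCC contradicts the intention-to-treat rule and can bias the 12-month comparison

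*Protocol article*

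**What the plan says.** The Statistical analyses section sets one rule for the whole trial: every child stays in the arm of allocation. The sentence begins "All analyses will be conducted using an “intention to treat” (ITT) analysis where all subjects will be compared in the groups which they were originally" and goes on to cover children who withdraw or are lost. It names the primary test but no time point: "Mann Whitney U test will be used to determine if differences in quality of life measures exist between the ICCC versus self-directed care groups".

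Under Safety considerations/patient safety, a different rule appears. "Children randomised to the self-directed pathway will be allowed to change to the ICCC pathway after 6 months, if they wish". The next sentence reads: "However, their recorded data at 12 months will not be used in the final analyses".

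Twelve months is a listed time point for the primary outcomes. The Outcome measures section begins "Primary outcome measures taken at 1 week, 3, 6, 12 months include", and the visit description has medical students telephone caregivers at 12 months for the quality of life modules, the distress scale and the locus of control questionnaire. The article does not call the exclusion a per-protocol or sensitivity analysis, and it defines no target effect that would justify it.

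**The concern.** The values in question are not missing. They are collected and then set aside because of something the family chose after randomisation. Only children in the self-directed arm can be removed in this way.

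The trial is unblinded, and families decide after six months of living with their allocation, so the decision may well reflect how the child is doing. At 12 months the control arm would then consist of the controls who did not want the intervention, compared with the whole ICCC arm. If struggling families switch, the remaining controls look better and a real ICCC benefit is understated. If the more engaged, better-faring families switch, the benefit is overstated.

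What is at stake is the longest follow-up. In the visit descriptions the quality of life modules are completed at 1 week, 6 months and 12 months, so 12 months is one of only two quality of life assessments after the first.

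**Working it through.** **1. The two rules side by side.** The general rule covers all analyses and states that "all subjects will be compared in the groups which they were originally assigned (regardless of withdrawal or lost to follow-up"). The specific rule removes the 12-month record of a child randomised to self-directed care who later changes pathway. For such a child, the first rule requires the 12-month value to be counted in the control arm and the second forbids using it. An analyst can follow only one.

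**2. Inputs for the illustration.**
- From Sample size and statistical power: "total sample size of 112 children (80% power to detect a mean effect difference of 15 between groups on the quality of life scale"), significance level 0.05, attrition 50%.
- From Randomisation: equal allocation.
- Assumed, because the article does not give them: the SD, a two-sided test, the share of controls who switch (s), and the correlation (r) between the tendency to switch and the 12-month score.

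**3. The plan's own figure.** 112 × 0.5 = 56 evaluable, or 28 per arm. Solving n = 2(1.96 + 0.842)² × SD² / 15² for n = 28 gives SD = 20.03. With SD 20, n = 2 × 7.849 × 400 / 225 = 27.9, rounded up to 28 per arm, and 56 / 0.5 = 112. SD 20 is therefore the value consistent with the plan, but it is inferred, not stated.

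**4. Shift of the control mean.** Suppose there is no true effect and the fraction s of controls lowest on the switching index is removed. The mean of those who remain rises by

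shift = SD × r × φ(z_s) / (1 − s),

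where z_s is the s-quantile of the standard normal distribution and φ its density. The factor φ(z_s)/(1 − s) is 0.195, 0.350, 0.497 and 0.798 for s = 10%, 20%, 30% and 50%. Multiplying by SD 20 gives:

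| Controls removed | r = 0.1 | r = 0.2 | r = 0.35 | r = 0.49 |
|---|---|---|---|---|
| 10% | 0.4 | 0.8 | 1.4 | 1.9 |
| 20% | 0.7 | 1.4 | 2.4 | 3.4 |
| 30% | 1.0 | 2.0 | 3.5 | 4.9 |
| 50% | 1.6 | 3.2 | 5.6 | 7.8 |

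The values 0.35 and 0.49 arise if switching correlates 0.7 with the 6-month score and the 6- and 12-month scores correlate 0.5 or 0.7 (0.7 × 0.5 and 0.7 × 0.7). If better-faring families switch, every shift keeps its size and changes sign. With r = 0 the shift is zero.

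**5. Effect on the planned test.** A simulation of the Mann-Whitney test (3,000 runs per setting, 28 per arm before removal, no true effect) gave a two-sided type I error of about 0.05 at r = 0 for every switching rate. At r = 0.5 it was about 0.08, 0.12 and 0.20 to 0.21 with 20%, 30% and 50% of controls removed.

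**6. Precision.** Two-sample t-test, standardised difference 15/20 = 0.75, non-centrality 0.75 × √(n₁n₀/(n₁ + n₀)), with n₁ = 28 in the ICCC arm:

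| Controls left (removed) | Power |
|---|---|
| 28 (none) | 78.7% |
| 25 (about 10%) | 76% |
| 22 (about 20%) | 73% |
| 14 (50%) | 61% |

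The normal approximation used in step 3 gives 80.1% for 28 per arm; the t-test figure is slightly lower. The planned test is Mann-Whitney, so the table is a guide to the relative loss.

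**The case against.** The strongest reply concerns reach. Switching is allowed only after 6 months, so the 1-week, 3-month and 6-month comparisons come before any exclusion. Neither the power statement nor the test description names 12 months as the decisive time point. This stands: the defect is confined to 12-month analyses.

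The second reply concerns size. A reader might infer that the exclusion does bias the 12-month result, perhaps by several points. The documents do not support that. They give no switching rate, no SD and no link between switching and outcome, so neither direction nor size can be derived. If switching is unrelated to outcome there is no bias, only fewer controls. This also stands, which is why the table includes weak selection and low switching. The 61% power figure is likewise an extreme case: it takes the full planned attrition and then has half of the remaining controls switch.

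Third, a reader might conclude that 6 months has to become the primary time point. That does not follow. It is a separate design choice, and it would move emphasis away from the longest follow-up.

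Finally, keeping the switchers has its own price. If ICCC works, controls who receive it late will narrow the 12-month difference. That is true, but it is a known feature of an as-randomised comparison and no reason to leave two incompatible rules in place.

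**Conclusion.** The contradiction is certain and rests on the wording alone. Following the exclusion sentence as written would remove a self-selected part of one arm at a listed primary-outcome time point. The consequence is a risk of bias of unknown size and direction, plus a certain loss of precision if anyone switches.

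Under an assumed SD of 20 and removal of 10% to 50% of controls, the shift is about 0.4 to 3.2 points for correlations of 0.1 to 0.2, and about 1.4 to 7.8 points for correlations of 0.35 to 0.49. As shares of the 15-point target these are roughly 3% to 21% (0.4/15 to 3.2/15) and 9% to 52% (1.4/15 to 7.8/15). These figures are conditional illustrations and do not predict what this trial will show.

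**What to change.** Delete the sentence in Safety considerations/patient safety that excludes the switchers' 12-month data. State in Statistical analyses that all recorded 12-month data are analysed in the arm as randomised, whether or not the child changed pathway. Record the date of each switch. If an estimate of the effect had nobody switched is wanted, present it only as a labelled sensitivity analysis, for example with values after the switch set to missing and multiply imputed from earlier data. The option to switch is left as it is. Naming 6 months as the primary time point is optional and not part of this correction.

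The cost is small but goes beyond wording. The 12-month values are already collected, so no new data are needed except the switch date. The 12-month contrast may be diluted by switching and should be described accordingly. Recruitment began in October 2017, so the change needs an amendment through the ethics committee named under Ethics approval, and a registry update if it counts as major. It should be settled before the 12-month results are examined, because choosing between the two rules with open-label data in view would invite selective reporting.

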### Trial status

This study is ongoing, with recruitment commenced in October 2017 and planned to continue for an 18 months period. It is planned that trial results will be published in relevant peer-review journals at the conclusion of the trial.

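### Dropping the 12-month data of controls who change to ICCC contradicts the intention-to-treat rule and can bias the 12-month comparison in either direction

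*Protocol article*

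**What the plan says.** - Safety considerations/patient safety opens a one-way change of pathway: "Children randomised to the self-directed pathway will be allowed to change to the ICCC pathway after 6 months, if they wish". The next sentence is "However, their recorded data at 12 months will not be used in the final analyses".
- Statistical analyses sets the general rule that "all subjects will be compared in the groups which they were originally assigned (regardless of withdrawal or lost to follow-up"). It applies this to all analyses and names a Mann-Whitney U test for the quality-of-life comparison.
- Outcome measures puts 12 months among the times for the primary measures: "Primary outcome measures taken at 1 week, 3, 6, 12 months include". No single primary time point is named.
- The 12-month contact is planned in both arms. Under the ICCC pathway, "medical students from each hospital will call the primary caregiver to complete: Peds QOL Child and Family Impact Modules", with the distress scale (SUDS) and Locus of Control. For the other arm, "The procedure for self-directed care pathway is similar to ICCC" apart from access to the liaison officer.
- Randomisation states that families know their allocation.

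**The concern.** The two rules give different 12-month analysis sets, and nothing in the article reconciles them by an exception, a separate estimand or a sensitivity analysis. The values at issue are not missing: the protocol describes them as recorded and then sets them aside.

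The exclusion applies to one arm only and follows a choice that families make unblinded, after six months' experience of their allocation. What remains at 12 months is ICCC completers against controls who preferred to stay.

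- If families who are doing badly change, the remaining controls look better and ICCC benefit is understated.
- If families who are doing well change, ICCC benefit is overstated and false claims of benefit become more frequent.
- If the choice is unrelated to outcome, there is no bias, only a smaller control group.

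**Working it through.** **Inputs from the protocol** (Sample size and statistical power): N = 112, 80% power, difference 15, significance level 0.05, 50% attrition. Completers: 112 × 0.5 = 56, or 28 per arm with the intended equal allocation.

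**Assumed, because the document gives no value:** two-sided testing; the SD; the share *s* of control completers who change; and the gap *D* between switchers and stayers in the 12-month score they would have under self-directed care.

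**Reproducing 112.** n per arm = 2(1.96 + 0.8416)² SD²/15². With SD 20 this is 2 × 7.849 × 400/225 = 27.9, so 28 per arm, 56 in total and 56/0.5 = 112. The planned size therefore fits an SD near 20. Solving the t-test exactly for 28 per arm and 80% power gives d = 0.762 and SD = 15/0.762 = 19.67, which is used below.

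**Bias from the exclusion.** The full control mean is s × (switchers' mean) + (1 − s) × (stayers' mean). If switchers lie D below stayers, the stayers' mean exceeds the full mean by s × D. If they lie D above, it falls short by s × D. For D = 10 the shift is 1.0, 2.5 and 5.0 points at s = 10%, 25% and 50%.

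**Two-sample t-test results** (an approximation to Mann-Whitney; control n = 28(1 − s), ICCC n = 28):

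| | s = 10% | s = 25% | s = 50% |
|---|---|---|---|
| Controls left | 25.2 | 21 | 14 |
| No selection: power for 15 | 78% | 73% | 62% |
| Switchers 10 worse: a true 15 appears as | 14.0 | 12.5 | 10.0 |
| – power | 72% | 58% | 33% |
| – no true effect: rejection favouring self-directed care | 3.8% | 6.3% | 11.5% |
| – no true effect: rejection favouring ICCC | 1.6% | 0.8% | 0.3% |
| – no true effect: total rejection | 5.4% | 7.2% | 11.8% |
| Switchers 10 better: a true 15 appears as | 16.0 | 17.5 | 20.0 |
| – no true effect: rejection favouring ICCC | 3.8% | 6.3% | 11.5% |

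The nominal rate in each direction is 2.5%. For other gaps, rejection in the favoured direction is 3.1%, 4.1%, 5.7% with D = 5 and 4.6%, 9.5%, 20.5% with D = 15.

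**Checks with the planned Mann-Whitney test, no true effect.**
- 8,000 simulated trials, 3, 7 or 14 of 28 controls dropped, the choice driven half by a low 6-month score, assumed 6-to-12-month correlation 0.5. The control mean rises by 1.3, 2.8 and 5.4 points and rejection is 5.7%, 7.5% and 12.4%. With correlation 0 there is no shift and rejection is 4.5% to 5.1%.
- A stronger assumption (SD 20, correlation of 0.6 in either direction between the tendency to change and the 12-month outcome): rejection is about 16–17% at 30% switching and about 30% at 50%.

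**Keeping switchers as randomised** (28 per arm). If they gain the full 15 points after changing, the expected difference is 15(1 − s) = 13.5, 11.25, 7.5 and power is 71%, 56%, 29%. If they gain half, it is 15 − 7.5s = 14.25, 13.1, 11.25 and power is 76%, 69%, 56%. With no effect of ICCC, early or late, and attrition unrelated to outcome, rejection stays at 5%.

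**The case against.** The exclusion has a legitimate aim. Once controls receive ICCC, their 12-month scores no longer show self-directed care, and setting aside post-change values is a recognised way to aim at a no-switch effect. The rule is prespecified, and it removes only 12-month values, so switchers still contribute their earlier data. That aim stands, but simple deletion meets it only if changing is unrelated to outcome, and it still breaks the intention-to-treat rule as worded.

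Other points on that side are fair:

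- With 50% attrition expected, neither arm is complete at 12 months. The comparison is between completers, and the exclusion adds a one-sided selection on top.
- Only 12 months is affected. It follows the coordinated GP appointments at 1 week, 3 and 6 months, and its weight in the primary analysis is not fixed.
- At 10% switching with a 10-point gap, the effect is small: 1.0 point and 5.4% rejection. Material distortion needs higher switching and a real gap, and the document supports no particular rate.
- Keeping switchers can dilute the contrast more than the exclusion does. With worse-off switchers and full gain, power is 71%, 56%, 29% as randomised against 72%, 58%, 33% under exclusion. The case for the change is validity, not power.

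None of these points removes the contradiction. A separate analysis plan could not settle it without departing from one of the two sentences.

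**Conclusion.** The concern holds. The two rules cannot both be followed at 12 months as written, and the one in the safety section makes a self-selected, unblinded, one-arm exclusion after randomisation at a listed primary-outcome time. That conclusion rests on the text alone.

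The size rests on assumptions. It runs from no bias, if changing is unrelated to outcome, to 5 points of a 15-point target and 11.5% false claims in one direction, if half of control completers change and differ by 10 points. The sign cannot be known in advance. Switchers' 1-week and 6-month scores would let the direction of selection be examined, but under the current rule their recorded 12-month values stay out of the final analyses. This should be corrected; it does not undermine the 6-month comparison.

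**What to change.** **Core change.** Replace the exclusion sentence with wording such as: *Children who change pathway remain in their randomised group in all analyses, including at 12 months; the number and dates of changes will be reported.* An analysis that sets aside post-change data can be kept as a sensitivity analysis, with switchers and stayers compared on their 1-week and 6-month PedsQL, SUDS and Locus of Control scores.

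**Useful additions, not required by the contradiction.** Allow a change only once the child's 6-month assessment is complete, since its window runs to 14 days after the due date. Name 6 months, the last assessment before switching opens, as the main quality-of-life comparison, and read 12 months as early versus optional delayed ICCC. Naming a main time point in an open trial already recruiting is a substantive amendment and needs its own justification.

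**Cost.** The core change is wording in the protocol, matching wording in any analysis plan and in the registry where they repeat the rule, and an ethics submission. It needs no extra visits or children, because the 12-month call is already planned in both arms. The price is the diluted 12-month contrast shown above.

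**Timing.** Trial status gives "recruitment commenced in October 2017 and planned to continue for an 18 months period" and the article appeared in February 2018. The first child could reach 6 months only around April 2018, so at publication the rule could still be changed before any switch.
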